## Instruments

- Structured Clinical Interview for DSM-IV Axis I Disorders (SCID-I) [47] for the diagnosis of mental disorders and collection of socio-demographic data, psychotropic drug consumption, and treatments received.
- Beck Depression Inventory, Second Edition (BDI-II) [48-49]. It is a 21-item self-report instrument to assess the existence and severity of symptoms of depression. It has good psychometric properties and acceptability. This is the main outcome measure.

- Clinical Outcomes in Routine Evaluation-Outcome Measure (CORE-OM) [50], a 34-item self-report questionnaire for the assessment of subjective well-being, symptoms or problems, life functioning and risk. It has good psychometric properties and it has been adapted into Spanish for free distribution recently [51]. The short version (SFB) of 18 items will be used for session-to-session monitoring of the therapy process.
- Hamilton Rating Scale for Depression (HAMD) [52] is the most widely used outcome measure in clinical trials for depression. It is a clinician-rated 17-items instrument with good psychometric properties.
- Repertory Grid Technique (RGT) [27] for assessing the presence, number and severity of cognitive conflicts. It is a semi-structured interview oriented at the elicitation of personal constructs and their assessment as they are applied to a set of significant others (for a more detailed description of the format used in this study see [36]). Other repertory grid measures assessing the construction of self and cognitive structure will be examined in another study.

## Treatments

*Group Cognitive Behavioral Therapy:* A comprehensive therapy manual [53] has been created for this study based in Beck's cognitive therapy manual [13] and two more recent publications [54, 55]. The manual has been adapted to 8 group sessions of approximately 120 minutes of length. This treatment will be applied to all patients in the study, led by two therapists, both licensed psychologists with sufficient experience and training to carry it out. The groups will be formed with 6-8 patients, and thus it is estimated that between 14 and 18 therapy groups will be conducted. Furthermore, once the seventh session is finished, patients will receive (following randomized allocation) one of the two types of individual psychotherapy compared in this study (CBT or DFT) by the same group therapists (one in each condition). Once this phase of individual sessions is done, another group CBT session lasting 180 minutes (with a break) will be scheduled. This final session, focused on relapse prevention, is thought to provide also a sense of continuity for all the therapy process and reunion of all patients and therapists involved.

*Individual Cognitive Behavioral Therapy:* Patients assigned to this condition will receive CBT following a complementary manual [56] based on the same sources as above. The manual has been adapted to 8 sessions of approximately 60 minutes and to the fact that patients have received group CBT previously. The therapist will also have conducted that group.

*Individual Dilemma Focused Therapy:* Patients assigned to this condition will receive DFT following the manual designed specifically for this project [57], based on Feixas and Saúl [41] and Senra, Feixas and Fernandes [42]. Since this type of intervention has never been tested before, the process for creating this manual followed the indications of Carroll and Nuro [58] for the development of therapy manuals. The therapy will consist of 8 sessions of approximately 60 minutes.

In DFT manuals (and in very general terms), the first session comprises welcoming and establishing rapport, analysis of demand, therapy goals definition, and identification of main dilemmas. Subsequently, feedback of the results of the evaluation is provided and the presenting problem(s) or symptom(s) is reframed in terms of the dilemma(s). Next, work on the dilemma(s) is conducted over several sessions, and the therapeutic process is completed with the revision of the work done on dilemma(s) and future prospects. During all phases, techniques originating from Personal Construct Therapy are used (see, e.g. [59]). As in the CBT condition, the therapist will have previously conducted group therapy with these patients.

## Procedure

Professionals of collaborating centers will be asked to inform their patients with major depression or dysthymia of the existence of this psychological treatment study and enable us to contact those who accept the opportunity to participate. For each center, an information sheet for potential participant patients and another for professionals with information on how to refer patients for the study were created. Finally, to reach a wider population range, a web page ([www.ub.edu/terdep](http://www.ub.edu/terdep)) and a flyer have been produced for the study. After referral by phone or email patients will be contacted to arrange for the selection and assessment process.

**Initial assessment** (T1) will be carried out in three phases. At first the nature of the study is explained and, if the patient agrees to participate and signs the informed consent, the BDI-II is applied, to verify the clinically significant presence of depressive symptoms (a score above 19). Second, patients meeting this criterion will be evaluated using the SCID-I interview to confirm the diagnosis of MDD or DD (if this is not the case, they will be excluded) and explore for other comorbid disorders. The section "Overview" included in this interview will also be used to collect socio-demographic data and information relative to previous treatments, to clarify that they are not receiving and will not receive any other concurrent psychological treatment, and to record psychotropic drug consumption. A few other instruments will also be used in this and further assessment sessions as part of another study. With patients selected in this phase a second assessment session will be scheduled in the following weeks. In this third phase, the CORE-OM and the RGT will be administered. The resulting data will be analyzed with the RECORD 5.0 software [27, 44]. In the following day, they will be contacted to confirm their inclusion in the study (if they have at least one cognitive conflict) or exclusion (in which case a way of providing the appropriate assistance to them will be sought together with the professionals from the center where they came from). The evaluators will be Psychology graduate students (or advanced undergraduates) who will have been specially trained to perform the entire assessment process, as in particular the SCID-I and the RGT interviews require specific training, and they will be, at this point, blind in regard to the treatment modality which will be assigned to the patients. Two evaluators will conduct the assessment process for each potential participant.

**Beginning of the treatment and randomization.** Once assessed and accepted for the study, patients will be summoned individually to a meeting with their therapists to explain the psychological treatment combining group and individual therapy, and then convened for the first CBT group session. In this meeting and at the beginning of the consecutive 16 therapy sessions, the CORE-SBF will be administered for routine evaluation of the therapy process and to monitor suicide risk. Whenever patients rate 3 or 4 on item 5 (suicide plans) they will be given especial attention after the group session for a more careful assessment of suicide risk as specified in the therapy manual.

Once the first phase of 7 group sessions is finished, they will be randomly assigned to one of the two individual treatment conditions (CBT or DFT) which will begin following the group therapy. Randomization will be done using permuted blocks with a random assignment online application [60] by a staff member of the Department of Personality, Assessment and Treatment of the University of Barcelona, completely oblivious to the study and blind to treatment conditions. Therefore, group CBT therapists can only know of patient allocation after the first phase of group treatment is completed, right at the moment they have to start individual therapy. In any case, therapists will not have participated in the initial evaluation of those patients nor will they in any subsequent assessments.

Treatments will be carried out mostly in the health centers corresponding to the patients according to the Catalan Public Health System, both in the common group format and in the two individual treatment conditions. If, eventually, the treatment cannot be carried on in these centers, patients will be invited to participate in the groups of ACTC. Groups will be formed in the various centers as soon as 8 patients have been admitted to the study and agree to initiate the proposed treatment.

Therapists will be graduate students enrolled in the master in Cognitive Social Therapy at the University of Barcelona. This is not a research oriented course but rather a three-year program designed to provide therapy training. Both group and individual sessions will be recorded on audio (a fact which is also reflected in the informed consent). This will allow supervision of each session from members of the team with more clinical experience who will evaluate the performance of the therapists in order to maximize their adherence to the relevant manual and ensure that therapy is being beneficial for its recipients. Before the start of the treatment, differentiated training workshops will be developed for each type of treatment to provide therapists with specific training in the protocols for individual and group therapy used in the study.

**Consecutive assessments, termination and follow up.** Once the individual therapy phase is terminated, a second assessment (T2) of all initial measures will be carried out by the same pair of evaluators who conducted the initial assessment (whenever possible), blind to the therapeutic condition of each patient. In the following week the final group session will take place and a more qualitative assessment session (as part of a complementary study) will take place in another week. There will also be follow-up assessments at three months (T3) and one year after (T4) completion of treatment, to check the degree of maintenance of the accomplished changes. Finally, one (or occasionally two) booster sessions will be offered to all patients during the fourth month after treatment termination.

**Treatment integrity.** For group CBT and the individual CBT arm of the study, therapist adherence will be assessed using the Revised Cognitive Therapy Scale (CTS-R). Because there are no pre-existing adherence/fidelity measures for DFT, a scale will be created to measure therapist adherence to this individual therapy arm.

Two trained clinical graduate students will independently rate a random selection of sessions using the CTS-R for the group sessions and both scales for the individual ones. Inter-rater reliability and success at discriminating between the content of the CBT and DFT will be computed. Patient's treatment compliance will be monitored by attendance and homework completion.

## **Statistical analyses**

All data derived from the measurements and the clinical data (including use of psychotropic drugs) and socio-demographic information will be entered into IBM Statistical Package for Social Sciences Version 20.0. The main statistical calculations will be performed on an intention-to-treat basis (patients will be analyzed as initially randomized). Preliminary normality tests will be performed for continuous variables which will be expressed as mean  $\pm$  standard deviation.

Analyses will include elementary head-to-head comparisons of the intervention groups as well as mixed models of repeated measures analysis of variance in which initial measures (baseline) of the dependent variables will be used as covariates. Sociodemographic and clinical differences

between patients (such as diagnosis of MDD or DD, chronicity) in response to treatment will be explored, as well as the potential mediator or moderator role of the cognitive measures obtained with the RGT, especially in regard to the number and intensity of cognitive conflicts. In fact, additional analysis will take these conflicts as a dependent variable to observe how they have varied with the different treatments. Also as secondary analyses, the inclusion of the CORE-OM/SFB in the study will allow the analysis of the degree of therapeutic change in other aspects, such as the patients' psychosocial functioning and subjective well-being. Moreover, it will also allow assessment of the change experienced in relation to the number of sessions and the percentage of change per session. In all the analysis which permit it, and depending on the variations found between the groups, patient drug consumption will be statistically controlled. In all statistical contrasts derived confidence intervals will be taken into account as well as their effect sizes.

Finally, we will calculate the proportion of patients with a reliable and clinically significant improvement on the BDI-II, HAMD-17 and CORE-OM outcome measures. We will follow Jacobson and Truax who established that clinical improvement is based on both reliable change (the extent to which pre-to-post-differences scores are reliable) and on clinical significant change (the extent to which post-treatment scores are clinically meaningful). Chi-square tests will be used to test the frequency differences in these categories between the two intervention groups.

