## Participants

Since this is the first controlled study of DFT, we don't have any previous data on which to base our estimations. But according to other studies comparing CBT with a variety of other therapies, we estimated medium between-group effects. Thus, to determine the sample size we calculated that with a statistical power of 0.80, considering a dropout rate of 20%, an  $\alpha$  significance level of 0.05 (two-sided) and an effect size of 0.30 we need a total of 112 patients. In terms of our primary outcome measure (BDI-II, see below) and based on Spanish normative data, calculation yielded a 3.3-point difference between groups.

*Inclusion Criteria:* All participants will meet diagnostic criteria for Major Depressive Disorder (MDD) or Dysthymic Disorder (DD) according to the DSM-IV-TR [46] and a score above 19 on the BDI-II questionnaire. Once the RGT is administered, only those patients who have at least one cognitive conflict are included in the treatment phase of the study, which based on previous data [39] it should be 90% of the cases. The age range is established between 18 and 70 years.

*Exclusion Criteria:* Patients presenting bipolar disorders, psychotic symptoms, substance abuse, organic brain dysfunction, acute suicidal ideation or mental retardation will be excluded from the study. Those who are receiving psychological treatment will not be accepted either, unless it is suspended at the time of inclusion in the study itself, in agreement with the patient and the therapist who is applying it. The presence of other comorbid conditions (anxiety, eating or personality disorders, etc.) and consumption of psychotropic drugs will not be cause for exclusion but they will be assessed and recorded for statistical control. Finally, those who do not have enough level of competence to communicate in Spanish or Catalan, or patients with substantial visual, hearing and cognitive deficits cannot be included.

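### Adjustment for psychotropic drug use depends on the between-arm difference found in the data and is not limited to pre-randomisation values

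*Protocol*

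**What the plan says.** - **The rule.** Protocol, Statistical analyses: "In all the analysis which permit it", and "depending on the variations found between the groups, patient drug consumption will be statistically controlled". No outcome is exempted, so the rule reaches the BDI-II, which Instruments names as the main outcome measure.
- **The contrast.** For the repeated-measures models the same section says that "initial measures (baseline) of the dependent variables will be used as covariates". Drug use has no such restriction to baseline.
- **Eligibility.** Participants: "consumption of psychotropic drugs will not be cause for exclusion but they will be assessed and recorded for statistical control". This gives the purpose of recording but no time point and no fixed covariate.
- **When drug use is recorded.** Procedure, Initial assessment (T1): the interview's overview section is used, among other things, "to record psychotropic drug consumption". Instruments likewise assigns drug consumption to the SCID-I. T1 precedes randomisation, which follows the seventh group session.
- **After randomisation.** Procedure, Consecutive assessments: "a second assessment (T2) of all initial measures will be carried out". Drug use is not named there, and the measures taken at T3 and T4 are not listed.

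**The concern.** Two features of the sentence are unsatisfactory.

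First, the trigger is the observed difference between arms. Under randomisation, a baseline difference in drug use arises by chance. How large it looks is a poor guide to whether the variable belongs in the model; its relation to the outcome matters more. With no threshold, variable or time point stated, the analyst can see both results before choosing one.

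Second, nothing confines the adjustment to values recorded before allocation. If post-randomisation values exist and are used, a difference caused by treatment could itself trigger the adjustment. The adjusted contrast would then no longer be the intention-to-treat comparison of the arms that the section sets out to make.

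At stake are the type I error and the meaning of the primary BDI-II estimate.

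**Working it through.** **Inputs.** The protocol gives no figure for this rule and no drug-use rates or correlations. From Participants: 112 patients, 20% dropout, two-sided alpha 0.05, power 0.80, effect size 0.30, 3.3 BDI-II points. Completers: 112 × 0.80 = 89.6, or about 45 per arm with 1:1 allocation assumed.

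**The plan's own figure.** With 0.30 read as Cohen's f (standardised difference 0.60), n per arm = 2 × (1.96 + 0.84)² / 0.60² ≈ 44, and 88 / 0.80 = 110. The t-based version needs 45 per arm, and 90 / 0.80 = 112.5. So 112 is reproduced on that reading. Read as a standardised difference of 0.30, it would take about 438. This does not decide the present point; it only supplies the 45 per arm and a plausible effect of 0.60 SD.

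**Check 1: baseline drug use, no treatment effect.** 10,000 simulated trials per row, 45 per arm, half of patients on drugs (assumed), r = correlation of drug use with outcome (assumed). Entries are type I error; the simulation error is about √(0.05 × 0.95 / 10,000) = 0.002.

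| r | always adjust | adjust if arms differ at p < 0.05 | take the smaller p-value |
|---|---|---|---|
| 0.2 | 0.049 | 0.049 | 0.058 |
| 0.4 | 0.052 | 0.044 | 0.071 |
| 0.6 | 0.050 | 0.041 | 0.078 |

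A mechanical trigger does not inflate the error. The freedom left by an unstated threshold can.

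**Check 2: post-randomisation drug use that follows residual severity.** Model: y = −0.60 × arm + N(0, 1); drug use = 1 if y + N(0, s²) > 0. A smaller s means a stronger link. The unadjusted mean is −0.60 throughout.

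- s = 1.5: always adjusted −0.485 (19% lost); adjusted if arms differ at p < 0.2, −0.51 (15% lost); at p < 0.05, about −0.54 (roughly 10% lost).
- s = 3: conditional rule −0.57 to −0.59 (2% to 5% lost).
- s = 1: always adjusted −0.41 (31% lost), with power falling from 0.80 to 0.62. The arms differ in drug use at p < 0.05 in about 34% of trials because of the treatment effect alone. I reran this link under the conditional rule: about 18% lost with a p < 0.05 trigger and 26% with p < 0.2. The 2% to 15% range therefore belongs to the two weaker links and is not an upper bound.

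The model omits the baseline outcome covariate that the protocol specifies, so these figures are illustrative.

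**Check 3: the opposite direction.** Assume drug uptake of 50% in the CBT arm and 30% in the DFT arm, drugs lowering the score by 0.5 SD, and a direct effect of −0.60 SD. The total effect is −0.60 + 0.5 × (0.50 − 0.30) = −0.50 (simulated −0.51). Adjusting returns −0.60, so the estimate moves away from zero.

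**The case against.** **Post-randomisation use is inferred.** Drug use is explicitly scheduled only at T1. The T2 sentence repeats the initial measures without naming drug use. Statistical analyses uses a similar phrase for baseline values of the dependent variables, so it may mean the outcome scales only. The design figure, which might settle this, is not shown. The differences found between groups can equally be read as baseline imbalance. This stands: a reader might infer that the plan will adjust for drug use at T2 to T4, but the text only leaves that open, and for T3 and T4 it does not list the measures at all.

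**On the baseline reading the harm is small.** This also stands for a mechanical rule, as check 1 shows. A statistical analysis plan could fix the threshold and the variable. It would still inherit a trigger based on observed balance, because the protocol itself states that trigger.

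**The direction is not fixed.** A reader might infer bias toward no difference. That holds when drug use merely follows residual severity; check 3 gives the reverse.

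**Points on the BDI-II.** It is tempting to turn the 15% loss into about 1 point by pairing 0.60 SD with an SD of 11. That mixes two readings: an SD of 11 comes from 3.3 / 0.30, and 0.60 × 11 = 6.6 points is twice the stated 3.3. With an effect of 0.30 SD (3.3 points), the loss at s = 1.5 is about 0.4 points with a p < 0.2 trigger and 0.2 with p < 0.05, and about 0.1 or less at s = 3.

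**Adjustment is not obligatory.** A prespecified unadjusted analysis would be equally valid under randomisation. That is right; the objection is to deciding after seeing the data. Controlling for drug use remains a legitimate aim.

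**Conclusion.** The concern holds as a defect in a rule that the protocol states, not as a detail left to a later plan. Adjustment of the BDI-II and other comparisons depends on between-arm differences found in the data, and it is not limited to values recorded before randomisation.

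- **Certain from the text:** the data-dependent trigger, its reach to the primary outcome, and the absence of a baseline limit that the outcome covariates do have.
- **Conditional on analyst discretion:** type I error of about 0.06 to 0.08, against 0.04 to 0.05 under a mechanical baseline trigger.
- **Conditional on drug use being re-recorded at T2 and used:** bias of unknown sign. The size rests wholly on assumed links: 2% to 15% of the effect lost under the conditional rule with weak to moderate links, and up to about one third with the strongest link simulated and adjustment in every case. The estimate grows if drugs lower scores and the comparison arm uses more of them.

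No single percentage or point loss can be attributed to this trial. The wording should be changed because closing the ambiguity is nearly free and the primary estimate is exposed to it.

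**What to change.** In Statistical analyses:

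1. Delete the clause that makes control for drug use depend on differences found between the groups.
2. Name one drug-use variable recorded at T1 (for example any psychotropic drug, yes/no) and enter it as a fixed covariate in the primary BDI-II model and the corresponding secondary models, whatever the observed balance.
3. State that the primary estimate is not adjusted for drug use recorded after randomisation, and that any such data are reported descriptively by arm.

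The cost is one sentence of wording and one degree of freedom in each model. The T1 data are already to be collected, and nothing in patient management changes.
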